# Evaluation of the Efficacy of the Traditional Chinese Medicine Formulation Ru-Yi-Jin-Huang-Saan on Colles Fracture After Surgery: Protocol for a Randomized, Double-Blind, Placebo-Controlled Trial

**DOI:** 10.2196/56849

**Published:** 2025-03-05

**Keywords:** traditional Chinese medicine, Ru-Yi-Jin-Huang-Saan, external application, Colles fracture, Patient-Rated Wrist Evaluation, PRWE, PRWE score, surgeries, fracture, randomized controlled trial, RCT, alternative treatment, postoperative, protocol, Western medicine, wrist evaluation, pain relief medication

## Abstract

**Background:**

Colles fracture, a common wrist injury, often requires surgical intervention. After surgery, patients may experience persistent pain and reduced wrist function, potentially resulting in long-term disability. In clinical practice, traditional Chinese medicine practitioners frequently use Ru-Yi-Jin-Huang-Saan (RYJHS) to treat such patients in Taiwan. RYJHS is a traditional Chinese herbal formula with a history spanning centuries, primarily used topically for the treatment of bone fractures and the promotion of healing. However, there is currently a lack of substantial clinical evidence supporting its efficacy in the management of postsurgical Colles fractures. To the best of our knowledge, there are no studies evaluating the clinical effectiveness of RYJHS.

**Objective:**

This study aims to investigate the therapeutic potential of RYJHS in postsurgical Colles fracture cases. An additional objective is to provide an alternative treatment option for postoperative patients unable to take anti-inflammatory and pain relief medications.

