**Methods:**

This is a protocol for a randomized, double-blind, placebo-controlled trial. A total of 100 postoperative patients with Colles fracture, aged 20-80 years, will be recruited for this study. They will be randomly assigned to either the experimental or control group in a 1:1 allocation ratio. Both groups will receive standard postoperative Colles fracture treatment. The primary outcome measure will assess wrist functional recovery using the Patient-Rated Wrist Evaluation score. Secondary outcomes will include C-reactive protein levels and ultrasound measurements of wrist swelling. All of these examinations will be assessed at baseline, 3 days after surgery, and 6 days after surgery. In addition, the Dyshidrotic Eczema Area and Severity Index will be used to monitor for adverse skin reactions.

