### Study Settings and Participants

All participants undergo standard medical treatment after surgery and are involved in the efficacy assessment of RYJHS external application. Figure 1 shows the study’s flowchart. Both groups apply a patch plaster on the back of the wrist without wounds (avoiding the suture of the fracture operation). Figure 2 shows the site of the medication application. The experiment group apply the RYJHS plaster, while the control group apply a placebo plaster. The patch is applied twice a day, for 6 hours each time, with a 6-hour break in between, repeated for 3 days, completing one course of treatment. Patients undergo two courses of treatment, with the first course completed during hospitalization, and the second course completed 3 days after discharge.

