### Inclusion Criteria

To be eligible for our study, patients must meet the following criteria: be 20-80 years of age, have a Colles fracture (Frykman classification type I-VI) [59] diagnosis that has been treated with open reduction and internal fixation (ORIF) surgery, and provide informed consent either personally or through their family members.

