### Exclusion Criteria

The following exclusion criteria will be applied: age older than 80 years or younger than 20 years; inability to comply with experimental procedures or complete questionnaires; presence of wounds on the back of the wrist; allergy to the herbal patch before; use of other Chinese herbal topical medicine after fracture; pregnancy; cancer; stroke; and systemic diseases such as severe anemia, thyroid disease, and poorly controlled diabetes.

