## Discussion

### Expected Findings

The primary clinical treatments for Colles fractures, such as closed reduction, casting, percutaneous fixation, external fixation, and ORIF, generally yield positive functional outcomes. However, both percutaneous and external fixation have reported a higher risk of infection, while percutaneous fixation has been shown to have a higher rate of soft tissue injuries [64,65]. Besides, the ORIF procedure including local dissection, reduction, and the insertion of plates or screws results in a higher incidence of tendonitis, tendon irritation, or tendon rupture [66,67]. In Taiwan, the routine conventional treatment for Colles fracture is ORIF surgery. However, operations often result in soft-tissue and lymphatic vessel damage. As a result, patients may experience heat, pain, redness, and swelling after the operation. The discomfort disrupts their willingness to undergo rehabilitation. Prolonged swelling can also affect the range of motion, hand function, muscle strength, and outward appearance of these patients [68]. Therefore, resolving pain and swelling is a significant problem for patients with Colles fracture after ORIF surgery.

The most common method of relieving swelling is ice packing. Ice packing can reduce swelling, capillary permeability, and delivery of inflammatory substances [69]. Besides, ice packing can decrease nerve conduction velocity, increase pain threshold, and provide analgesia [70]. However, many studies have reported that ice packing not only delays wound healing but also has a higher risk of cold injury [71,72]. Besides, pain management is also a concern for patients who undergo ORIF surgery. Physicians often prescribe opioids; NSAIDs; or a combination of opioids, NSAIDs, and steroids for pain management [73]. However, due to the potential side effects, these medications raise concerns for patients with diabetes, hypertension, gastrointestinal disorders, impaired liver function, or impaired kidney function.

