### Conclusion

This randomized, double-blind, placebo-controlled trial aims to provide robust evidence of the efficacy and safety of RYJHS as a topical adjunctive treatment for postsurgical Colles fractures. With the potential to reduce inflammation and aid functional recovery, RYJHS could offer an alternative, nonpharmaceutical option for managing postoperative complications in patients with Colles fractures.

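### The objective of offering an alternative for patients who cannot take anti-inflammatory or analgesic drugs does not match an add-on design in unselected patients; only an adjunct claim can be supported

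*Protocol article*

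**What the plan says.** The Objective paragraph of the Abstract first states the main aim, the therapeutic potential of RYJHS after Colles fracture surgery, and then adds: "An additional objective is to provide an alternative treatment option for postoperative patients unable to take anti-inflammatory and pain relief medications".

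On background care, the Abstract Methods say "Both groups will receive standard postoperative Colles fracture treatment", and Study Settings and Participants says "All participants undergo standard medical treatment after surgery and are involved in the efficacy assessment of RYJHS external application". The randomised contrast is then given: "The experiment group apply the RYJHS plaster, while the control group apply a placebo plaster".

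On who is enrolled, Inclusion Criteria asks for age 20-80, consent, and that patients "have a Colles fracture (Frykman classification type I-VI) [59] diagnosis that has been treated with open reduction and internal fixation (ORIF) surgery". Exclusion Criteria has nothing on intolerance of, or contraindication to, analgesics, and ends with "systemic diseases such as severe anemia, thyroid disease, and poorly controlled diabetes".

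On usual pain control, Expected Findings says: "Physicians often prescribe opioids; NSAIDs; or a combination of opioids, NSAIDs, and steroids for pain management".

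On the claim to be made, the Conclusion first describes RYJHS as an adjunctive topical treatment and then says that "RYJHS could offer an alternative, nonpharmaceutical option for managing postoperative complications in patients with Colles fractures". The last paragraph of Expected Findings also uses the adjunctive description.

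**The concern.** An aim labelled as an objective should be answerable from the trial. This one concerns a particular group (patients who cannot take certain drugs) and a particular use (in place of those drugs). The design appears to supply neither.

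What is at stake is the reach of the conclusion. If the trial is positive, a reader of the Abstract and Conclusion could take it as evidence that RYJHS can stand in for anti-inflammatory or analgesic medication. An add-on comparison does not provide that evidence. The document also describes the product in two ways, as adjunct and as alternative, and only the first fits the comparison made.

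**Working it through.** No figure in the document bears on this point and no calculation decides it. The check sets the objective against each part of the design.

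**1. Which effect is estimated.** Write Y(r, a) for the mean outcome with RYJHS (r = 1) or placebo (r = 0), and with drug treatment for pain and inflammation given (a = 1) or not given (a = 0). Take standard treatment to include such drugs. This is an inference from the Introduction and Expected Findings, because the document does not itemise standard treatment. Then:

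- Trial contrast: Y(1,1) − Y(0,1), the add-on effect.
- Effect in patients who cannot take the drugs: Y(1,0) − Y(0,0).
- Effect of RYJHS in place of the drugs: Y(1,0) − Y(0,1) = [Y(1,0) − Y(0,0)] − [Y(0,1) − Y(0,0)].

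The first equals the second only if the effect of RYJHS is the same with and without the drugs. The trial cannot check this, since a is not randomised and no arm is defined by it. The third also needs the effect of the drugs themselves, Y(0,1) − Y(0,0), and there is no drug comparator from which to estimate it. If drug use varies between patients under standard care, the trial contrast becomes an average over whatever they take. That is still neither of the other two effects.

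**2. Which patients are enrolled.** The inclusion criteria cover age, fracture type with surgery, and consent. None concerns ability to take analgesics. Expected Findings names diabetes, hypertension, gut disease and poor liver or kidney function as conditions in which the drugs raise concern. Exclusion Criteria removes poorly controlled diabetes and, through an open-ended phrase, other systemic disease. The remaining conditions are not named as exclusions, so some such patients may enter. They would enter unselected and in unknown number, and a condition that raises concern is not the same as inability to take the drug.

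**3. Which data and analysis are listed.** Outcome Measurements lists gender, age, affected and dominant hand, PRWE, CRP, ultrasound, x-ray and DASI. Table 2 adds medical history at screening and adverse events. Neither lists analgesic, anti-inflammatory or other concomitant medication. Statistical Analysis names no outcome based on drug use and no subgroup of patients unable to take the drugs. Its regression adjusts for covariates that it does not name.

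**4. Result.** Steps 1 and 2 are enough to show the mismatch. Step 3 shows that nothing listed would fill the gap, but the conclusion does not depend on it.

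**The case against.** The strongest reply is that the sentence is a motivation rather than a hypothesis. It speaks of providing an option, it appears as an objective only in the Abstract, and no outcome or test is attached to it. The aim at the end of the Introduction is to evaluate efficacy and adverse effects after surgery, which the design does address. The article already uses adjunctive wording in the Discussion and Conclusion, and the sentence about an alternative is hedged and does not mention patients unable to take drugs. For a study that describes itself as close to phase 2, a placebo-controlled add-on comparison is a reasonable first step.

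Much of this stands, and it keeps the point to one of scope. It does not remove the point: the text calls the sentence an objective, and the Conclusion repeats the word alternative beside the word adjunctive.

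A reader might go further and infer any of three things. The document does not support them.

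- *Analgesic use is not collected.* The list in Outcome Measurements is introduced as non-exhaustive, and a condensed article commonly leaves concomitant medication to the full protocol or case report form. All that can be said is that it is not among the items listed there or in Table 2.
- *Every participant receives analgesics.* Standard treatment is not itemised. What the document reports is what physicians often prescribe, not the trial's regimen.
- *A real benefit will be hidden by a given number of PRWE points because placebo patients take more analgesia.* That direction is plausible, but the document gives no figure for drug use or for its effect on PRWE, so no size can be put on it. Drug use after randomisation is also part of the treatment effect under usual care, which is a legitimate quantity to estimate in a blinded randomised trial.

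**Conclusion.** The point holds as a mismatch between a stated objective and the design. The trial can support a statement about RYJHS as an adjunct to standard postoperative care. It cannot support a statement about replacing medication, or about patients who cannot take it.

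The size is one objective in the Abstract and one sentence in the Conclusion. Randomisation, the primary comparison on PRWE and the sample size are unaffected. The conclusion rests on standard treatment being given to both arms and on the absence of any eligibility criterion about drug intolerance; both are plain in the text. That standard treatment includes analgesics is an inference, though a likely one. Without it, the lack of selection and of any drug comparator would still leave the objective unanswered. This should be corrected, but it is not a flaw that threatens the trial.

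**What to change.** Restate the additional objective in the Abstract, and the sentence on an alternative nonpharmaceutical option in the Conclusion, as an adjunct to standard postoperative care. Draw no conclusion about replacing medication or about patients who cannot take it. This costs only wording.

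If the full protocol does not already record analgesic and anti-inflammatory use, abstract inpatient use from the charts, assuming that they hold it, including for patients already enrolled. Ask about home use at the day 6 assessment of patients who have not yet passed it. Report use descriptively by arm beside PRWE. Do not enter it as an adjustment covariate: it arises after randomisation and may itself be affected by treatment. The regression's unnamed covariates should be specified so that it is left out.

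The downside is some extra data work and incomplete home data. The first patient was enrolled on June 15, 2023, and 32 were enrolled by December 2023. The article appeared on March 5, 2025, 56 days before the projected end of recruitment on April 30, 2025 (26 days left in March plus 30 in April). Home use may therefore be obtainable for only a minority, which is a further reason to keep this descriptive. Nothing in the care given needs to change.

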**Methods:**

This is a protocol for a randomized, double-blind, placebo-controlled trial. A total of 100 postoperative patients with Colles fracture, aged 20-80 years, will be recruited for this study. They will be randomly assigned to either the experimental or control group in a 1:1 allocation ratio. Both groups will receive standard postoperative Colles fracture treatment. The primary outcome measure will assess wrist functional recovery using the Patient-Rated Wrist Evaluation score. Secondary outcomes will include C-reactive protein levels and ultrasound measurements of wrist swelling. All of these examinations will be assessed at baseline, 3 days after surgery, and 6 days after surgery. In addition, the Dyshidrotic Eczema Area and Severity Index will be used to monitor for adverse skin reactions.

**Results:**

This protocol was registered at ClinicalTrials.gov on December 6, 2022. It was performed in accordance with the approved guidelines and regulations of the participating institutions. Recruitment began in May 2023, with data collection expected to conclude in May 2025. Study completion is expected in December 2025.

**Conclusions:**

This is the first protocol discussing the assessment of the therapeutic efficacy and safety of topical traditional Chinese medicine in patients after fracture surgery. The protocol will establish an integrated care model combining both traditional Chinese medicine and Western medicine for postsurgical fracture cases.

**Trial Registration:**

ClinicalTrials.gov NCT05638360; https://clinicaltrials.gov/ct2/show/NCT05638360

**International Registered Report Identifier (IRRID):**

DERR1-10.2196/56849

## Introduction

Distal radial fracture is the most common fracture clinically and is approximately one-sixth of cases in emergency departments in the United States [1]. Studies on the Taiwanese population have shown that the prevalence of Colles fracture was 10.2-14.5 per 10,000 people [2]. This situation causes huge losses to the social economy, as well as decreased school attendance, lost work hours, care needs, and permanent disability [3]. In the Western world, closed reduction and cast immobilization are the first choices of treatments in most cases of distal radius fracture [4]. However, surgery intervention is the first choice in Taiwan. Unfortunately, pain and swelling after surgery may hinder rehabilitation and the regaining of hand function, such as postponed recovery of range of motion, daily function, and muscle power [5]. To control pain and swelling, physicians often use ice packing [6], opioids, nonsteroidal anti-inflammatory drugs (NSAIDs), and steroids [7-9]. Some studies reported that these drugs can have the risk of addiction, lead to respiratory restriction, delay fracture wound healing, raise the risk of osteoporosis, and raise glucose levels [10-13]. Since internal medicine has side effects, external medicine should be used to reduce swelling and relieve pain after the operation.

Traditional Chinese medicine (TCM) has been used to treat fractures for thousands of years. In animal studies, TCM extracts have been shown to accelerate bone healing and prevent delayed fracture healing and nonunion [14]. Other studies have also shown that TCM inhibits the inflammatory response in osteoarthritis rat models [15,16]. Until now, there has been no published study on the application of TCM in the treatment of postoperative fractures. However, TCM for external application has been widely used to treat swelling and pain after fracture. Therefore, we have designed an experiment to verify the curative effect of the external application of TCM in fracture surgery.

Ru-Yi-Jin-Huang-Saan (RYJHS) is a TCM herbal patch composed of a fixed blend of TCM ingredients combined with water. It is traditionally applied to relieve swelling and pain in the early stages of musculoskeletal injuries, attributed in TCM theory to its heat-clearing and swelling-reducing properties. Modern pharmacological studies also confirm its antibacterial, anti-inflammatory, wound-healing, and hemostatic effects [17,18]. As recorded in the classic TCM text, *The Golden Mirror of Medicine*, RYJHS is prescribed for conditions such as furuncles, carbuncles, traumatic wounds, mumps, contact dermatitis, lower limb edema, mastitis, and cellulitis. An animal study also demonstrated that RYJHS significantly accelerated fracture healing, notably enhancing collagen formation and bone cell metabolism [19].

The primary components of RYJHS include *Trichosanthis radix, Rhei radix et Rhizoma, Phellodendri cortex, Curcumae longae rhizoma, Angelicae dahuricae radix, Magnoliae cortex, Glycyrrhizae radix et Rhizoma, Citri reticulatae pericarpium vetum, Atractylodis rhizoma*, and *Arisaematis rhizoma*. Pharmacological research highlights the various therapeutic properties of these components (given in Table 1). For example, *Trichosanthes kirilowii* extract has been shown to accelerate wound healing and possesses antibacterial and anti-inflammatory effects [20-22]. *Rhei radix et rhizoma* inhibits inflammation via NF-κB inactivation [23], and *Phellodendri cortex* has both anti-inflammatory and antibacterial properties [24,25]. Curcumin, the active component in *Curcumae longae rhizoma*, exhibits antioxidant, antimicrobial, and wound-healing effects through growth factor induction [26]. Studies on *Angelicae dahuricae radix* highlight its antinociceptive and anti-inflammatory activities [27]. *Magnoliae cortex*, rich in magnolol, is noted for its anti-inflammatory and antimicrobial activities [28-38]. *Glycyrrhizae radix et rhizoma* has shown anti-inflammatory effects through inhibition of PGE2, TXB2, and LTB4 [39], along with antimicrobial properties [40-42]. *Citri reticulatae pericarpium vetum* offers significant antioxidant and anti-inflammatory benefits [43-46]. *Atractylodis rhizoma* demonstrates antifungal, antibacterial, antioxidant, and anti-inflammatory activities [47-50], while *Arisaematis rhizoma* has been found to have anti-inflammatory and analgesic effects [51,52].

**Table 1 table1:** The proportion of Ru-Yi-Jin-Huang-Saan (RYJHS) and the efficacy of its ingredients.

*Latin crude drug name* (English name)	Plant part	Proportion	Efficacy
*Trichosanthis radix* (Trichosanthes root)	Root	25%	Wound healing, antibacterial, and anti-inflammatory effects
*Rhei radix et rhizoma *(Rhubarb)	Root and rhizome	12.5%	Anti-inflammatory effect
*Phellodendri cortex* (Phellodendron bark)	Bark	12.5%	Antibacterial and anti-inflammatory effects
*Curcumae longae rhizoma* (Turmeric rhizome)	Rhizome	12.5%	Wound healing, antioxidant, radical scavenging, antimicrobial, and anti-inflammatory effects
*Angelicae dahuricae radix* (Dahurian Angelica root)	Root	12.5%	Antinociceptive and anti-inflammatory effects
*Magnoliae cortex* (Magnolia bark)	Bark	5%	Anti-inflammatory and antimicrobial effects
*Glycyrrhizae radix et rhizoma* (Liquorice root and rhizome)	Root and rhizome	5%	Anti-inflammatory and antimicrobial effects
*Citri reticulatae pericarpium vetum* (Aged tangerine peel)	Peel	5%	Antioxidant and anti-inflammatory effects
*Atractylodis rhizoma* (Atractylodes rhizome)	Rhizome	5%	Antifungal, antibacterial, antioxidant, and anti-inflammatory effects
*Arisaematis rhizoma* (Jackinthepulpit tuber)	Rhizome	5%	Anti-inflammatory and analgesic effects

Further research indicates that RYJHS can alleviate inflammatory pain without causing sensitization [53]. Clinically, it is used to manage conditions such as phlebitis [54], osteoarthritis of the knee [55], gout, diabetic foot ulcers [56], and herpes zoster.

However, despite the numerous studies mentioned above, there is still a lack of clinical research on RYJHS. This study aims to evaluate the efficacy and adverse effects of using RYJHS on Colles fracture after surgery.

## Methods

### Study Design

The study is a randomized, double-blind, placebo-controlled trial design based on SPIRIT (Standard Protocol Items: Recommendations for Interventional Trials) reporting guidelines (Multimedia Appendix 1) [57], and the results will follow the CONSORT (Consolidated Standards of Reporting Trials) guidelines [58]. Our research project is scheduled to recruit patients from May 1, 2023, to April 30, 2025. All postoperative patients with Colles fracture will be recruited through referrals from orthopedic physicians at Changhua Christian Hospital. Researchers will screen and select participants based on specific inclusion and exclusion criteria. In this study, all participants are randomly assigned using a computerized block randomization schedule. We randomly generate a pool of 100 patients, who are assigned to sequentially numbered opaque envelopes. The treatment allocations are balanced within each group, with each group containing 50 patients. Researchers and patients are both blinded to the treatment allocation, with the exception of the statistician responsible for the randomization process. The two groups in the study consisted of the experimental group receiving RYJHS treatment and the control group receiving a placebo.

